# Fistulotomy versus standard cannulation as the primary technique for all patients undergoing ERCP with a native papilla: a protocol for a single center randomized controlled trial

**DOI:** 10.1186/s13063-022-06084-4

**Published:** 2022-02-16

**Keywords:** ERCP, Pancreatitis, Post-ERCP pancreatitis

## Abstract

**Background:**

Endoscopic retrograde cholangiopancreatography (ERCP) is an indispensable procedure for the management of pancreaticobiliary diseases. Post-ERCP pancreatitis (PEP) is the most common serious adverse event. One risk factor of PEP is difficulty achieving biliary access. The conventional ERCP technique involves the cannulation of the bile duct via the ampulla of Vater, followed by sphincter incision using electrocautery. Conventionally, if the standard method fails then, precut techniques have been utilized as an alternative means of gaining biliary access. The needle-knife fistulotomy (NKF) technique involves identifying the intra-duodenal segment of the bile duct and uses a needle knife to incise directly into the bile duct. This is done above and away from the natural office, thus minimizing thermal damage which may result in PEP. Our recent prospective study of 50 patients demonstrated the safety and feasibility of the NKF precut technique as a primary means of gaining biliary access. The next step is to conduct a randomized controlled trial to compare the efficacy and safety of initial NKF to the standard cannulation in a non-selective patient population undergoing ERCP.

**Methods:**

A randomized control trial of 538 consecutive, non-selective patients with pancreaticobiliary disease undergoing ERCP at a tertiary care center in Kingston, Ontario, Canada, will be conducted. Patients will be randomized to one of two treatment groups, standard cannulation or NKF. The primary outcome of the study will be the incidence of PEP. Secondary outcomes will include rate of successful cannulation of the common bile duct (CBD), time to successful cannulation, total procedure time, difficulty of cannulation, and incidence of complications.

**Discussion:**

This RCT will yield important answers regarding the efficacy and safety of initial NKF to the standard cannulation in a non-selective patient population undergoing ERCP. The results of our study could alter ERCP practices and outcomes if NKF is shown to reduce PEP risk.

**Trial registration:**

ClinicalTrials.govNCT04559867. Registered on September 23, 2020

## Background

Since its inception in 1968, endoscopic retrograde cholangiopancreatography (ERCP) has become an indispensable procedure for the management of pancreaticobiliary diseases [1]. Six years later, the first endoscopic sphincterotomies were completed by Kawai and Claussen and it is now used for indications including, but not limited to, stone removal from the common bile duct (CBD), management of papillary stenosis, or type 1 sphincter of Oddi (SOD) dysfunction and to facilitate the delivery of pancreaticobiliary therapy [2, 3]. The procedure, however, continues to result in significant morbidity in a small but not insignificant number of patients. Post-ERCP pancreatitis (PEP) is the major source of this, affecting between 5 and 7% of patients undergoing the procedure [2]. For 10% of patients who experience PEP, it can be severe and even fatal [3].

One risk factor of PEP is difficulty achieving biliary access. Factors include but are not limited to increased time to cannulation, increased number of cannulation attempts, and pancreatic duct cannulations. Although medical interventions such as intravenous volume expansion, pancreatic protease inhibitors, and NSAIDs have shown promise or even benefit, the risk of PEP persists [4–11]. Therefore, any intervention or technique that can minimize or even eliminate post-ERCP pancreatitis is highly desired.

The conventional technique involves the cannulation of the bile duct via the ampulla of Vater, followed by sphincter incision using electrocautery [12, 13]. This opens the distal end of the bile duct, allowing easier access for stents and removal of larger objects such as stones. It has been reported, however, that standard access techniques fail between 5 and 10% of the time [2]. If the standard method fails, then conventionally, precut techniques have been utilized as an alternative means of gaining biliary access. There are various precut techniques used to gain access to the common bile duct (CBD), which include needle-knife fistulotomy (NKF), needle-knife sphincterotomy (NKS), and trans-pancreatic precut sphincterotomy (TPS) [14, 15].

Needle-knife fistulotomy involves identifying the intra-duodenal segment of the bile duct and uses a needle-knife to incise directly into the bile duct. The fistula is away from the native orifice of the papilla. NKS involves using a needle knife to cut starting at the native orifice and incising upwards to expose the bile duct opening. A TPS involves incising the pancreatic sphincter, which lies adjacent to the biliary sphincter (within the native orifice), to expose the biliary opening.

Numerous studies have demonstrated that adverse event rates are comparable between methods when precut sphincterotomy is conducted by an expert endoscopist [16] and that moving to precut techniques earlier in the procedure can be associated with fewer adverse events [17–19]. With respect to which of the three techniques to employ, the NKF theoretically offers the lowest risk of pancreatitis as the incision is performed directly into the intra-duodenal segment of the bile duct, minimizing any contact or thermal damage to the pancreatic duct. This theory is supported by the results in the series by Jin et al., who observed a 0% incidence of pancreatitis using the NKF method as the initial technique for cannulation in high-risk patients [20]. Additionally, our recent prospective study of 50 patients demonstrated the safety and feasibility of the NKF precut technique as a primary means of gaining biliary access [21]. Without a control group, however, our trial could not compare the current results to the standard cannulation technique.

The next logical step then is to conduct a randomized controlled trial (RCT) to compare the efficacy and safety of initial NKF to the standard cannulation in a non-selective patient population undergoing ERCP. The objective of this study is to add to the literature of ERCP that assesses NKF as the initial method of gaining biliary access. The primary outcome of the study will be the incidence of PEP. Our hypothesis is that NKF will have a lower PEP rate than standard cannulation.

## Methods

### Study design and setting

This protocol (version 2.4) was written and reported according to the Standard Protocol Items: Recommendations for Interventional Trials (SPIRIT) recommendations [22], and a SPIRIT checklist is provided in the supplemental materials. This is a randomized, controlled, superiority trial comparing NKF to standard sphincterotomy for the primary endpoint of PEP. Secondary outcomes will further compare the safety and efficacy of the two methods. The study will take place at a single, tertiary ERCP referral center in Kingston, Ontario, Canada. All procedure will be performed by two experienced endoscopists having performed over 1000 ERCPs. The flow of participants is summarized in Fig. 1.

**Fig. 1 Fig1:**
[figure not shown]
Flow of participants

### Outcome measurements and definitions

The primary outcome of the study will be the incidence of PEP, defined as abdominal pain consistent with acute pancreatitis and an elevation greater than three times the upper limit of normal of serum lipase levels [23].The secondary outcomes of the study include:
Rate of successful cannulation of the CBD, with technical success determined by a cholangiogram;Inspection time; defined as time from visualization of ampulla to appearance of needle knife or sphincterotome;Time to successful cannulation, measured as follows:
i.Standard cannulation group (group I): time of endoscopic visualization of the sphincterotome on the screen to contact with the papilla orifice;ii.NKF group (group II): time of endoscopic visualization of the metal point of the needle knife on the screen to successful CBD cannulation as evident by the cholangiogram or wire advancement into the CBD;Total procedure time, measured for completed procedures from the time of esophageal intubation to the time of scope withdrawal from the patient mouth,Ampullary morphology—cannulation success and pancreatitis ratesDifficulty of cannulation, graded on a 3-point scale, based on the operator’s subjective opinion (easy, moderately difficult, very difficult), and,Incidence of complications graded and defined by Cotton et al. [20], notably, intra-procedural bleeding that required intervention (cautery, clips, or injection of epinephrine), delayed or sustained bleeding requiring transfusion or repeat endoscopy and immediate or delayed perforation.

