### Inclusion/exclusion criteria

Five hundred thirty-eight consecutive patients meeting inclusion/exclusion criteria, undergoing biliary ERCP by two expert endoscopists, will be considered for inclusion.

*Inclusion criteria*:
Patients, ages > 18, with an intact ampulla undergoing ERCP for therapeutic purposes who can provide informed consent. This includes patients who have confirmed choledocholithiasis on imaging and those who have a high suspicion of it based on imaging and lab values. Patients with and without a high suspicion for cholangitis will be eligible for the study. Other indications include the following: other benign biliary duct diseases including strictures, primary sclerosing cholangitis, and Mirizzi syndrome requiring biliary decompression. Furthermore, patients with suspected diagnosis of biliary leak following cholecystectomy will also be considered for enrollment in this study.Ability to read and understand the English language,Ability to follow-up in a reliable manner.

*Exclusion criteria*:
Bleeding disorder (Von Willebrand disorder, platelet count < 100,000, or INR > 1.5),Therapeutic level anticoagulation with low molecular weight heparin (LMWH), warfarin, or a direct-acting oral anticoagulant (DOAC),P2Y12 inhibitors not held for 5 days prior to the procedure,Prior biliary sphincterotomy,Concurrent pancreatitis (with inability to tolerate oral intake and requiring pain management),Altered upper GI tract anatomy (e.g., prior gastric bypass surgery such as Roux-en-Y or Billroth 2 gastrojejunostomy),Inability to achieve adequate sedation,Evidence of malignant infiltration of the ampulla or peri-ampullary area,NFK or standard cannulation is thought not to be feasible.Pregnancy,Operator inability to identify and access the intra-duodenal portion of the bile duct,Presumptive diagnosis of sphincter of Oddi dysfunction,Inability to access intraduodenal segment due to altered anatomy (e.g., ampulla within deep diverticulum),Requirement for pancreatogram or pancreatic intervention,Inability to provide informed consent.

*Recruitment plan:*

Three groups of patients will be approached for consideration of inclusion in this study:
Inpatients at Kingston Health Sciences Centre (KHSC) requiring an ERCP,Clinic patients, for whom an ERCP will be scheduled at a future date,Patients admitted from outside hospitals or out-patients requiring an ERCP.

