### Procedure

After obtaining consent, baseline patient characteristics (age, sex, indication for ERCP, preprocedure blood work including ALP, bilirubin, INR, hemoglobin and lipase) and the suspected diagnosis will be documented. The ERCP procedure will follow standard practice for patient preparation, sedation, and intubation of the duodenum. Patients will not be blinded to their treatment group. Patients will receive sedation in the form of midazolam, diazepam, fentanyl, and/or dimenhydrinate. Diclofenac will be administered per rectum at the conclusion of the procedure.

Access to the CBD will be attempted via either NKF or a standard sphincterotome. Upon identification of the ampulla, the operator will evaluate the feasibility of performing both the needle-knife fistulotomy and standard cannulation. If both approaches are feasible, then participants will be randomized with a 1:1 allocation to one of two treatment groups using a central online randomization program (Randomizer for Clinical Trials app, Medsharing, France) and block randomization. The block sizes will not be disclosed to ensure concealment. Should the operator determine that they are unable to safely perform one of the approaches, then the participant will not be randomized. Allocation concealment will be ensured, as the online randomization program will not reveal the treatment group until the endoscopist confirms both approaches are feasible.

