### Initial data collection and data management

Pre-procedure demographics, as well as lab results of liver enzymes, total bilirubin, lipase, international normalized ratio (INR), hemoglobin, platelets, and the white blood cell count will be recorded. The physician will document any abdominal pain and/or tenderness, both for severity and location. The suspected diagnosis will be documented along with radiologic findings.

Intra-procedure data collection will include total sedation used, sedation start time, endoscope insertion time, visualization of the ampulla, visualization of needle knife or sphincterotome on the screen, time of the sphincterotome making contact with papilla orifice, time of successful cannulation of the bile duct, time for remaining interventions, time of scope out of mouth, and administration of diclofenac. Each procedure will be recorded for verification purposes.

Other data recorded includes the following: ampullary morphology, difficulty of cannulation, normality/abnormality of the CBD, CBD stent placement, cannulation of the pancreas, pancreatic stent placement, pancreatic contrast injection, and any intraprocedural complications.

Post-procedure data will include assessment for pain/ pancreatitis at 24 h post-procedure. If the subject is an inpatient, this will include clinical assessment. If the subject is an out-patient, then they will be contacted by phone and questioned regarding abdominal pain. Should the subject report abdominal pain consistent with pancreatitis, they will be advised to come to the nearest emergency room for assessment as per current standard of care. A post-procedure day 7 phone call will also be scheduled, and subjects will be questioned regarding abdominal pain. Any post-procedure complications will be recorded as previously outlined. Outcome assessors will not be blinded to the treatment group.

Data will be inputted electronically by a full-time research assistant and stored and managed on a secure encrypted program.

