### Statistics and sample size

For the sample size calculation, we assume a PEP incidence of 7% with standard cannulation and expect a decrease to 2% in the fistulotomy group. Therefore, 538 patients will be needed (269 in each group) to assess the hypothesis with 80% power and an alpha of 0.05%.

The primary outcome will be assessed in an intention to treat principle. In addition, we plan to report on the number of patients that switched to NKF or standard cannulation following randomization. Primary and secondary outcomes will be assessed using regression methods. A log-binomial model will be used to generate an adjusted relative risk with 95% confidence intervals for the primary outcome. Linear regression models will be used for the secondary outcomes where appropriate. Normally distributed variables are presented as means with standard deviation (SD) and compared using Student’s *t*-test. Non-normally distributed variables are presented as medians with interquartile range (IQR) and compared with the Mann-Whitney-Wilcoxon test. Based on our pilot study, lost to follow-up is not expected to be an issue [21]. For less than 5% loss to follow-up, a complete case analysis will be done. For more than 5% loss to follow-up, multiple imputation and complete case sensitivity analyses (all combinations of the extremes of what could have occurred) will be done. Multiple imputation will be done in SPSS statistical software with all variables missing listed and five imputed datasets will be created.

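### The written definition of post-ERCP pancreatitis can count pancreatitis that was already present, because it asks for neither new or worse pain nor a rise from the pre-procedure lipase

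*Protocol article*

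**What the plan says.** The protocol article, under Outcome measurements and definitions, gives the primary outcome as "abdominal pain consistent with acute pancreatitis and an elevation greater than three times the upper limit of normal of serum lipase levels". Neither part is tied to the patient's state before the procedure.

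Under Inclusion/exclusion criteria, existing pancreatitis is an exclusion only in a qualified form: "Concurrent pancreatitis (with inability to tolerate oral intake and requiring pain management"). Stone disease is a main indication: "This includes patients who have confirmed choledocholithiasis on imaging and those who have a high suspicion of it based on imaging and lab values".

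The data needed for a before-and-after comparison are largely planned. The Procedure section lists "preprocedure blood work including ALP, bilirubin, INR, hemoglobin and lipase". Initial data collection and data management adds "The physician will document any abdominal pain and/or tenderness, both for severity and location". The same section sets the follow-up: "Post-procedure data will include assessment for pain/ pancreatitis at 24 h post-procedure", then a telephone call on day 7. It also states "Outcome assessors will not be blinded to the treatment group".

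For the sample size, the Statistics and sample size section says "we assume a PEP incidence of 7% with standard cannulation and expect a decrease to 2% in the fistulotomy group". The effect measure is an adjusted relative risk from a log-binomial model.

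**The concern.** The outcome definition and the exclusion do not fit together. A patient with stones, pain and a lipase already above three times the upper limit of normal, who can still eat, is not excluded by the pancreatitis criterion. That patient can satisfy both parts of the written outcome before the endoscope is inserted. If pain and raised lipase persist at the follow-up assessment, the criteria as printed are met although the technique caused nothing.

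Two consequences follow, and they are alternatives for any given case:

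- If the written rule is applied literally, events unrelated to technique enter both arms at about the same rate. The relative risk moves toward 1, variance rises and power falls.
- If assessors instead set such cases aside as pre-existing, they do so without a written rule and knowing the allocation. Randomisation does not protect against a difference between arms in those decisions.

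The trial is sensitive to this because few events are expected: 0.02 × 269 = 5.4 in the fistulotomy arm. The sample size is also set at almost exactly 80% power, with no reserve.

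**Working it through.** **Inputs from the protocol article (Statistics and sample size; Procedure).** Event rates p₁ = 0.07 (standard) and p₂ = 0.02 (fistulotomy); n = 269 per arm; 1:1 allocation; 80% power. Alpha is printed as 0.05%. I use two-sided 0.05, because that reproduces the stated size; 0.0005 would need 1282 patients in total.

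**Step 1: reproduce the plan's figure.** Two-proportion z-test, pooled variance under the null, no continuity correction, p̄ = (p₁ + p₂)/2:

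n = [1.960·√(2p̄(1−p̄)) + 0.8416·√(p₁(1−p₁) + p₂(1−p₂))]² / (p₁−p₂)²

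- p̄ = 0.045, so √(2 × 0.045 × 0.955) = 0.2932
- √(0.0651 + 0.0196) = 0.2910
- n = (0.5746 + 0.2449)² / 0.0025 = 268.7, rounded up to 269 per arm, 538 in total

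This matches the plan. Power at 269 per arm is 80.05%, and the planned relative risk is 0.02/0.07 = 0.286.

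**Step 2: add pre-existing cases.** Let f be the share of patients in each arm who meet the written definition through pancreatitis already present. The documents do not give f, so it is an assumption. The model also takes 7% and 2% to be rates of procedure-related events only. Then

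p₁* = f + (1−f) × 0.07 and p₂* = f + (1−f) × 0.02

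Power = Φ{ [(p₁*−p₂*)·√269 − 1.960·√(2p̄*(1−p̄*))] / √(p₁*(1−p₁*) + p₂*(1−p₂*)) }

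**Worked case, f = 1%.**

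- p₁* = 0.01 + 0.99 × 0.07 = 0.0793
- p₂* = 0.01 + 0.99 × 0.02 = 0.0298
- Relative risk = 0.0298/0.0793 = 0.376
- Power = Φ[(0.0495 × 16.40 − 0.6295)/0.3193] = Φ(0.571) = 71.6%

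**Results.**

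| Assumed f | Such patients per arm (269f) | Rates | Relative risk | Risk difference (points) | Power at 538 | Total N for 80% |
|---|---|---|---|---|---|---|
| 0 | 0 | 7.0% v 2.0% | 0.29 | 5.00 | 80.0% | 538 |
| 0.5% | 1.3 | 7.5% v 2.5% | 0.33 | 4.98 | 75.7% | 598 |
| 1% | 2.7 | 7.9% v 3.0% | 0.38 | 4.95 | 71.6% | 660 |
| 2% | 5.4 | 8.9% v 4.0% | 0.45 | 4.90 | 64.1% | 784 |

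The absolute difference is (1−f) × 5 points and hardly moves. The loss lies in the relative risk and in the added variance. At f = 2% the pre-existing cases would equal in number the procedure-related events expected in the fistulotomy arm (5.4 each).

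**Step 3: the other limit.** If the 7% and 2% already contain such cases at the rate the trial will see, the observed rates are the planned ones and no power is lost against the plan. The true loss lies somewhere between that limit and the table, and the documents do not say where.

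**The case against.** The strongest case on the other side is that new onset is already implied. The outcome is the incidence of an event named for following ERCP, and the definition cites a source that may carry onset and baseline criteria. The article condenses a longer protocol, and rules for a raised baseline lipase may stand there. This limits the claim: such cases can be counted, not that they will be. It does not remove it. The article states its operative criteria, and taken literally they can classify a non-event as an event.

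Several stronger readings are tempting and not supported:

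- **That there is no time frame.** Pain and pancreatitis are assessed at 24 h and again on day 7. What is missing is a link between those contacts and the definition.
- **That baseline lipase and pain go unused.** The covariates of the adjusted model are not listed, so lipase may be among them. Adjustment, however, would not change which patients are counted as events.
- **That the dilution is large.** An affected patient must have active pancreatitis at ERCP, escape the exclusion, still have compatible pain afterwards, and still have lipase above the threshold when tested. Outpatients are sent for assessment only if they report such pain. Nothing in the documents shows how often all of this occurs.
- **That the result is biased toward fistulotomy.** Equal misclassification in both arms does not raise the type I error. Unblinded discounting could bias in either direction, and the documents give no sign of which.

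It is also fair to say that a new-or-worsened criterion would still be judged by unblinded assessors. A written rule anchored to recorded baseline values narrows that discretion without abolishing it.

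**Conclusion.** The point holds in a limited form. As written, the outcome definition and the qualified exclusion together allow pancreatitis present before the procedure to be counted as PEP in either arm, or to be discounted without a rule by assessors who know the allocation. If f is 0.5% to 2%, the expected relative risk moves from 0.29 to between 0.33 and 0.45, and power from 80% to between 76% and 64%. These figures rest on an assumed f, on equal misclassification in both arms, and on planning rates that exclude such cases; the loss shrinks to nil as that last assumption fails. The z-test stands in for the planned log-binomial model.

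A reader might infer that the primary comparison is invalid. The documents do not support that: the affected group is narrow, its size is unknown, and the absolute difference is nearly preserved. This should be fixed because it concerns what the primary outcome counts and most of the data needed are already collected.

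**What to change.** Reword the primary outcome as new or worsened abdominal pain after the procedure, consistent with acute pancreatitis, with onset by the existing day 7 contact, and a post-procedure lipase above three times the upper limit of normal. For patients whose recorded baseline lipase already exceeds that threshold, also require a rise over baseline by a stated numeric amount. The trial team must set that amount before analysis, without reference to results by arm, and apply it identically in both arms; the documents give no basis for choosing it here. Add a sensitivity analysis that leaves out patients whose baseline lipase exceeded the threshold. Eligibility and patient care need not change.

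Costs: slightly fewer counted events, and a formal amendment during recruitment, which by the Trial status section began on December 1, 2020. Baseline lipase and the severity and location of baseline pain are already recorded. To judge worsening, pain should be recorded in the same terms at the 24 h and day 7 contacts.

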To perform the NKF, the ampulla will be identified and closely examined to accurately delineate the infundibulum. A needle knife (Needlecut 3 V, Olympus Medical Canada, Markham, Ontario) will be used to make a 2–3-mm incision in the mid to proximal third of the vertical axis in the intra-duodenal segment of the bile duct. The needle will be used to cut through the mucosa with intermittent examination for the muscular ampullary complex and subsequent penetration into the bile duct usually signaled by bile flow. When bile is seen, the fistula will be gently probed with a guidewire until the CBD is cannulated. Cannulation of the CBD will be confirmed with proximal advancement of the guidewire and contrast injection with cholangiography. If the findings on the cholangiogram indicate that further interventions are necessary, then the fistulotomy site will be extended with the use of standard sphincterotome or balloon sphincteroplasty as per operator. Further interventions include placement of metal or plastic biliary stents, brushing of the ducts for cytology, balloon dilation of strictures, intraductal cholangioscopy basket retrieval of stones, and balloon sweeping of the CBD.

The standard cannulation will be performed using a traditional sphincterotome (Clever-cut 3 V, Olympus Medical Canada, Markham, Ontario) with access gained to the biliary system via the native orifice (group I).

The operator will switch approaches under the following circumstances: [1] the patient was randomized to the sphincterotomy group (group I), but cannulation is not achieved in 10 min or [2] the patient was randomized to the NKF group (group II), but the operator is unable to achieve biliary access and feels they cannot safely cut further.

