### Safety reporting

The risks of NKF are similar to standard technique for ERCP. It is possible that there are unforeseeable risks associated with this procedure.

The reporting investigator will complete the serious adverse events (SAE) report, including date of event, admissions, diagnosis details, and date of discharge. SAEs will be reported to the Research Ethics Board (REB), where in the opinion of the principal investigator (PI) the event was:
“related”: that is, it resulted from administration of any of the research procedures;and“unexpected”: that is, the type of event is not listed in the protocol as an expected occurrence.

Reports of SAEs that are both related and unexpected will be submitted to the REB within 2 days of the PI becoming aware of the event.

A data safety monitoring board comprised of three gastroenterologists independent to the study with no competing interests will be reviewing the adverse events and enrollment every 50 cases. The study will be prematurely terminated should there be a significantly increased complication rate associated with needle-knife technique (over 20% of cases) or should successful cannulation of the CBD be less than 80%.

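### Successful bile duct cannulation is defined differently for the success rate and for the NKF time, and the standard arm's time ends at papilla contact, so the two arms' times share no end event

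*Protocol article*

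**What the plan says.** Four places in the protocol article bear on this.

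- **Outcome measurements and definitions, success rate (both arms).** The outcome is the "Rate of successful cannulation of the CBD, with technical success determined by a cholangiogram".
- **Outcome measurements and definitions, time to successful cannulation.** For group II (NKF) the interval ends at "successful CBD cannulation as evident by the cholangiogram or wire advancement into the CBD". For group I (standard) the interval is the "time of endoscopic visualization of the sphincterotome on the screen to contact with the papilla orifice".
- **Procedure.** For NKF: "Cannulation of the CBD will be confirmed with proximal advancement of the guidewire and contrast injection with cholangiography". The switch in group I applies if "cannulation is not achieved in 10 min", with no criterion for cannulation.
- **Safety reporting.** The study is to end early "should successful cannulation of the CBD be less than 80"%, again with no criterion and without naming an arm.

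Initial data collection and data management lists the moment of papilla contact and, as a separate item, the "time of successful cannulation of the bile duct". It does not say which sign marks the second. It also says that each procedure is recorded for verification.

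**The concern.** The success rate and the time to success describe the same event and should agree on who had it. Here the rate needs a cholangiogram, the NKF time accepts a cholangiogram or a wire, and the NKF procedure text describes both. The set of patients with a time to success can then differ from the set counted as successes.

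The time outcome has a second and larger problem. A time comparison between arms needs the same start and the same finish. Both clocks start when the instrument appears on the screen, but one stops when the sphincterotome touches the papilla and the other when the duct is reached. The first is only the beginning of the attempt. At stake is the interpretation of two secondary efficacy outcomes in an open-label trial whose outcome assessors are unblinded. A third outcome, cannulation success by ampullary morphology, inherits the ambiguity.

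**Working it through.** **The plan's own figure.** The document gives no number for cannulation success or cannulation time. The only figure needed is the group size. From Statistics and sample size, "we assume a PEP incidence of 7% with standard cannulation and expect a decrease to 2% in the fistulotomy group". With pooled variance, two-sided alpha 0.05 and 80% power:

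n = [1.960·√(2·0.045·0.955) + 0.842·√(0.07·0.93 + 0.02·0.98)]² / 0.05² = (0.5746 + 0.2449)² / 0.0025 ≈ 268.7, so 269 per group.

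This matches the plan. (Alpha is printed as 0.05%; that is a separate matter.) The 269 serves below only as a denominator.

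**Step 1: the criteria side by side for an NKF patient.**

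| Wire in CBD | Cholangiogram | Success rate | NKF time end | Procedure text (both signs) |
|---|---|---|---|---|
| no | no | failure | no time | not confirmed |
| no | yes | success | time | not confirmed |
| yes | no | failure | time | not confirmed |
| yes | yes | success | time | confirmed |

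The third row is the conflict between the rate and the time. The second row separates the rate from the procedure text only if a cholangiogram is obtained without wire advancement, a sequence that the Procedure section does not describe.

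**Step 2: when the NKF clock stops.** Even in the last row the stop time is not fixed. The either/or wording allows the clock to stop at the wire, whereas confirmation as described is complete only after contrast injection.

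**Step 3: the standard group's clock.** Contact with the orifice has to come before the duct is entered through that orifice. Two consequences follow from the text alone.

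- Every group I patient whose papilla is touched has a time to successful cannulation, including one who is never cannulated. A patient switched after 10 minutes without cannulation still carries a contact time from before the switch.
- The group I interval omits the whole attempt between contact and duct entry. The group II interval includes the corresponding work. The comparison as written shortens the standard arm's time.

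**Step 4: illustrative size of the classification problem.** The inputs are assumed. Let 95% of 269 NKF patients reach wire access, and let a fraction f of these lack a cholangiogram. The number classified differently is 269 × 0.95 × f, and the cholangiogram-based rate is 0.95 × (1 − f).

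| f | Patients | Success rate |
|---|---|---|
| 0 | 0 | 95.0% |
| 1% | 2.6 | 94.1% |
| 5% | 12.8 | 90.3% |
| 10% | 25.6 | 85.5% |

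**Step 5: illustration for the 80% limit.** All inputs are assumed: 25 NKF cases (half of a 50-case board review), 90% access by either sign, and 2, 5 or 8 percentage points of wire-only access. Observing under 80% means at most 19 successes in 25. The binomial probability is 3.3% at 90%, and 7.1%, 16.2% and 28.8% at 88%, 85% and 82%. This shows only that the choice of criterion could matter to the limit. It does not estimate what will happen.

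**The case against.** The best reply is that the texts can largely be reconciled. The Procedure section describes an operative sequence and does not define an outcome. It plans a cholangiogram after wire access in NKF cases, and further intervention depends on what that cholangiogram shows. A wire-only NKF case would depart from the described procedure and should be rare. The wording in the NKF time item can also be read as naming the visible sign that stamps the time, with the cholangiogram deciding success.

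Much of this stands. The group classified differently is probably small, and the real wording conflict is the either/or in the NKF time item against the cholangiogram criterion for the rate. But the document does not say that times count only in cholangiogram-confirmed successes. Nor does the reply touch the papilla-contact end event.

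Three stronger readings are tempting, and the documents do not support them.

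- A reader might infer that the looser criterion belongs to the experimental arm only and so flatters NKF. For time this is wrong: papilla contact is earlier and looser than either NKF sign, so the text as written favours the standard arm.
- A reader might try to compute a false-positive rate for the time comparison from the lag between wire and cholangiogram. No passage stops the standard arm's clock at a cholangiogram, and the document gives neither a lag nor a standard deviation.
- A reader might treat the 80% limit as a rule on early NKF cases. Safety reporting sets a review every 50 cases but gives neither an arm nor a denominator for that limit.

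It is also no gap that the standard-arm procedure text lacks its own confirmation step. The cholangiogram criterion for the rate covers both arms, and an article may condense procedural detail.

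**Conclusion.** The point holds in two parts.

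1. Success for the rate (cholangiogram) and the end of the NKF time (cholangiogram or wire) are inconsistent, so a wire-only NKF patient is a failure with a time to success. The extent is unknown and probably small if the described procedure is followed. The 3 to 26 patients shown rest on an assumed 95% access and an assumed 1% to 10% without a cholangiogram.
2. The two arms' times to successful cannulation share no end event. This follows from the text without any assumption. It is the larger defect, and its direction is to shorten the standard arm's time.

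The affected outcomes are secondary, and the PEP comparison and its sample size are untouched. The correction should still be made before analysis, because the same undefined term also governs the switch in group I and early termination.

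**What to change.** State one definition of successful CBD cannulation and use it in both arms, for the success rate and for the end of the time interval. For example: the time of first guidewire advancement into the CBD, confirmed by the subsequent cholangiogram. It must replace both the papilla-contact end event for group I and the either/or alternative for group II; changing only one still leaves no common end event. State also that accesses without a confirming cholangiogram are scored the same way in both arms.

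The 10-minute switch and the 80% termination limit use cannulation without a criterion. The investigators should reconcile those passages with the definition. Which criterion should apply to either rule is not proposed here.

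The cost is an edit to the outcome definitions. A time of successful cannulation is already on the data list. Recruitment began in December 2020 and the list does not say which sign that stamp marks, so times already recorded may need checking against the procedure recordings, as far as these show the event. A few wire-only accesses may be scored less favourably.
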